## Abstract

**Introduction:**

Primary ciliary dyskinesia (PCD) is a rare, genetic, multiorgan disease with an estimated prevalence of 1 in 10 000. It affects mainly the upper and lower airways due to impaired mucociliary clearance. Almost all patients have sinonasal or otologic (ear–nose–throat, ENT) problems, although the ENT clinical phenotype may present great variability. Despite that, data on PCD ENT manifestations are scarce and based on small single-centre studies. To date, we know little about the spectrum and severity of PCD ENT disease, its association with lung disease, its course over life and its determinants of prognosis.

This study protocol describes the aims and methods of the first prospective, observational, multinational cohort study focusing on ENT disease in patients with PCD.

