## Introduction

Primary ciliary dyskinesia (PCD) is a rare genetic, multiorgan disorder affecting approximately 1:10 000 individuals.^1 2^ Mutations in disease-causing genes result in defects in ciliary structure or function, leading to a wide range of symptoms from different organ systems.^3–5^ The clinical phenotype of the disease is heterogeneous; however, reduced airway mucociliary clearance predisposes almost all affected individuals to recurrent upper and lower respiratory infections.^6 7^

Persistent symptoms from the upper airways and ears (ear–nose–throat: ENT) are a common characteristic of most patients with PCD. Ear symptoms commonly present in children with PCD as severe and bilateral otitis media with effusion (OME).^8–11^ OME usually resolves spontaneously in otherwise healthy children, but in PCD it seems to persist longer and might need specific management.^8 12–15^ In some cases, persistent OME may lead to hearing impairment and cause delays in speech development.^16 17^ A newly published study evaluated 47 children in two PCD centres in North America and found that 52% of children with PCD-related hearing loss were not aware of their hearing deficit that was present on audiological assessment.^18^ While otologic involvement seems to improve with age in patients with PCD, sinonasal disease appears to persist and may worsen in adulthood.^19^ First manifestations appear sometimes soon after birth and are usually non-specific in the form of rhinitis and episodic facial pain due to recurrent infections leading gradually to chronic rhinosinusitis (CRS).^20–24^ In adults, a recent study identified sinonasal disease as a primary cause of decreased quality of life (QoL) in patients with PCD.^19^ Hypoplasia and agenesis of paranasal sinuses have also been described, while nasal polyps are more common in patients with PCD compared with the general population, although this complication has not been well characterised.^19 25 26^

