Finally, we will analyse follow-up data on ENT symptoms and examinations to describe the short-term course of sinonasal and otologic disease during a 2-year follow-up, and identify determinants of disease prognosis. Here, outcomes of interest will be the severity of CRS (based on a symptoms score), loss of smell, bacterial colonisation of the upper respiratory tract, need of surgical management of the sinuses, recurrent otitis media, OME, hearing impairment and need of surgical management of the ears. We will first describe how the outcomes change over the follow-up time in binomial or multinomial (for outcomes with more than three categories, such as hearing impairment) mixed models, using separate models for each outcome. Then, we will study determinants of disease prognosis categorising patients in four groups for each outcome based on the evaluation at baseline and at 2-year follow-up: (a) patients who never reported the outcome, (b) patients negative for the outcome at baseline but positive at follow-up, (c) patients positive at baseline but negative at follow-up and (d) patients positive at both time points. We will use mixed-effects multinomial regression models, including all possible determinants as fixed effects. We will select possible determinants from characteristics available at baseline, including symptoms and measurements; age at diagnosis, ultrastructural defects and genetic mutations; and general patient characteristics, such as age and sex. We will make our determinants selection based on directed acyclic graphs, considering existing literature. Data will be collected prospectively and in a standardised way resulting in small data heterogeneity between participating centres; however, we will still need to account for possible differences between countries in all analyses. Thus, we will analyse all outcomes of interest using random-effects models that account for clustering of patients within participating centres.

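### For the two graded outcomes (CRS severity and hearing impairment), the four-group prognosis analysis pools patients who worsen or partly improve without crossing the cut-off with patients who are stable

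*Protocol article*

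**What the plan says.** In the protocol article, *Planned analysis and outcomes of interest*, the follow-up analysis has two steps.

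- **Description.** Change over follow-up is modelled separately for each outcome, in binomial or "multinomial (for outcomes with more than three categories, such as hearing impairment) mixed models".
- **Determinants of prognosis.** This step proceeds by "categorising patients in four groups for each outcome based on the evaluation at baseline and at 2-year follow-up". The first two groups are patients who never had the outcome and patients who became positive. The other two are "c) patients positive at baseline but negative at follow-up and (d) patients positive at both time points". The model is then fixed: "We will use mixed-effects multinomial regression models, including all possible determinants as fixed effects".

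Eight outcomes are listed. The list opens "outcomes of interest will be the severity of CRS (based on a symptoms score), loss of smell" and goes on to bacterial colonisation, sinus surgery, recurrent otitis media, otitis media with effusion, hearing impairment and ear surgery. *ENT examinations* says that audiometry is recorded in WHO hearing loss grades.

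On frequency and course, the abstract says "Almost all patients have sinonasal or otologic (ear–nose–throat, ENT) problems", and the *Introduction* says that "sinonasal disease appears to persist and may worsen in adulthood". *Study objectives* (c) is to identify determinants of course and prognosis.

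**The concern.** The determinant step makes no exception for graded outcomes and does not divide the persistently positive group by change in severity. CRS is listed as a severity, yet it is analysed by a rule that keeps only which side of a cut-off the patient is on. Hearing impairment is treated as multi-category in the descriptive step and becomes positive or negative in the next.

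A patient whose hearing loss goes from mild to severe, with both grades counted as positive, is placed with patients whose hearing has not changed. So is a patient who improves without reaching negative. Objective (c) asks what predicts the course of disease. For these two outcomes the analysis could say what predicts crossing the cut-off, but not what predicts other change. A null result for a determinant would not bear on deterioration among patients already affected.

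**Working it through.** The plan has no figure of its own to reproduce. The expected 450–550 patients rest on feasibility, and no alpha, power or effect size is stated. The structural point follows from reading the text. Its size can only be illustrated on assumed inputs.

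**Step 1: what the classification retains.** For a score X at baseline and Y at 2 years, with cut-off t, the group depends only on whether X > t and whether Y > t. Any change with X and Y on the same side of t leaves the patient in (a) or (d), together with unchanged patients. This holds wherever t lies.

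**Step 2: group sizes.** Assumed: baseline prevalence p, incidence 20% among negatives, remission r of 10–20% among positives. From the document: N = 450–550.

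- New cases: (b) = N × (1 − p) × 0.20. For example, 450 × 0.20 × 0.20 = 18.
- Persistently positive: (d) = N × p × (1 − r). For example, 450 × 0.80 × 0.90 = 324, which is 72% of 450.

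| Assumed prevalence | (b), N = 450 | (b), N = 550 | Share of patients in (d) |
|---|---|---|---|
| 30% | 63 | 77 | 24–27% |
| 50% | 45 | 55 | 40–45% |
| 80% | 18 | 22 | 64–72% |
| 90% | 9 | 11 | 72–81% |

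**Step 3: how much change stays within a group.** Assumed: X and Y are standard bivariate normal with correlation 0.5, 0.7 or 0.85, with no average drift. The cut-off t is set so that a proportion p is positive, and it is the same at both visits. A change is |Y − X| ≥ 0.5 SD. There were 1,000,000 simulated patients per setting.

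Share hidden in (d) = P(X > t, Y > t, |Y − X| ≥ 0.5) / P(|Y − X| ≥ 0.5). The denominator is 0.62, 0.52 and 0.36 for the three correlations.

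| Assumed prevalence | Changes that stay in (d) (correlation 0.5 / 0.7 / 0.85) | Changes that cross into (b) or (c) |
|---|---|---|
| 30% | 11% / 14% / 17% | 41% / 34% / 28% |
| 50% | 27% / 30% / 34% | 47% / 39% / 32% |
| 80% | 62% / 65% / 68% | 32% / 27% / 22% |
| 90% | 78% / 80% / 82% | 20% / 17% / 14% |

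The remainder lies in (a), below the cut-off on both occasions. At 30% prevalence and correlation 0.5 this is 100 − 11 − 41 = 48%. A higher cut-off therefore moves uncounted change from (d) to (a) and does not remove it. Whether change below the cut-off matters depends on where the cut-off is put.

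**The case against.** Much of the opposing case is fair.

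- **Prevalence.** It would be tempting to infer that almost every patient is positive for CRS at baseline, so that the never and newly positive groups would be nearly empty. The document does not support this. The abstract's statement covers any sinonasal or otologic problem and gives no prevalence for a single outcome. The cohort takes all ages, and the *Introduction* describes CRS as developing gradually.
- **Expected course.** A reader might also infer that worsening among affected patients is the course the authors expect. The *Introduction* says only that sinonasal disease may worsen, and in adulthood, whereas the analysis covers 2 years. The same sentence says otologic involvement seems to improve with age, and group (c) does capture full resolution.
- **The descriptive step.** Change is not invisible to the whole study, because the multinomial models can describe shifts in hearing grade. The loss is confined to the analysis of determinants.
- **Cut-off.** If positive means above a severity threshold, some worsening falls in (b) and is counted. The threshold may be set in an analysis plan that is not shown, and its absence is not held against the article. But no single threshold registers change on either side of itself.
- **Scope.** For present/absent outcomes such as otitis media with effusion or need of surgery, the four groups are standard and informative. The criticism does not extend to them.
- **Exploratory aim.** The sample size section calls the analyses partly exploratory. That does not restore information the classification removes.

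**Conclusion.** The point holds for two of the eight outcomes and for the determinant step only. For CRS severity and hearing impairment, worsening or partial improvement that does not cross the cut-off is pooled with stability, so its determinants cannot be identified under objective (c). This comes from a method the article states, not from a detail left out.

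The size cannot be fixed from the document. On the assumed latent-score model, the share of changes of at least 0.5 SD that stay in the persistently positive group is modest if the outcome is uncommon (11–17% at 30% prevalence). It is about a third or a little less at 50% (27–34%), and most of them at 80% (62–68%) and 90% (78–82%). These figures rest on normality, an unchanged cut-off, no average drift, correlation 0.5–0.85 and a chosen 0.5 SD. Some of the simulated change would in practice be measurement noise. This is an inexpensive improvement to the plan and does not invalidate the study.

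**What to change.** - **Present/absent outcomes:** keep the four groups and the multinomial model.
- **Hearing impairment:** model the 2-year WHO grade with baseline grade in the model, either as an ordinal outcome or as worse, same or better.
- **CRS severity:** model the 2-year symptoms score with baseline score in the model, linear or ordinal according to the scale of the score.
- **Both:** keep centre as a random effect, as the article already intends for all outcomes. Account for a change of questionnaire version (the symptom questionnaire has three age-specific versions, with parent report below 14 years) or of audiometry type between visits.

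The cost is analysis wording. The symptom questionnaire is completed at every visit, and audiometry is a minimum requirement at all centres, with small exemptions such as for very young patients. The downsides are that these two outcomes are reported in a different format from the other six, and that small shifts may partly reflect measurement or a change of version.

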## Ethics and dissemination

Ethical approval to share pseudoanonymised patient data was obtained locally at each participating centre (online supplemental file). Written informed consent will be obtained in accordance with the national/local data protection laws, from patients aged 14 years or more (might differ per country based on local laws) or from the patient’s parents/caregivers for younger patients. Patients can withdraw their consent and their data from the study at any time by contacting the clinical team at each participating centre.

10.1136/bmjopen-2021-051433.supp1Supplementary data

The results of the study will be published in scientific journals and presented at scientific conferences to raise awareness about upper respiratory disease in patients with PCD.

The principal investigator of the study affirms and upholds the principle of the participants’ right to dignity, privacy and health and that the project team shall comply with applicable privacy laws. Especially, anonymity of the participants shall be guaranteed when presenting the data at scientific meetings or publishing them in scientific journals. Individual participant medical information obtained during this research project is considered confidential and will not be disclosed to third parties. Data will not be deposited at an open access repository. Because of the rarity of the disease although data will be pseudonymised, it may include still sensitive information; therefore, participants will not be asked to give consent to have their data deposited publicly.

### Patient and public involvement

Several patient support organisations were consulted and support the study. The EPIC-PCD is set up and can be further developed in the framework of the BEAT-PCD clinical research collaboration (CRC) network supported by the ERS.^42^ The BEAT-PCD CRC is a large multidisciplinary network, which includes more than 500 researchers and clinicians from more than 30 countries. The EPIC-PCD is part of the BEAT-PCD research portfolio, which ensures widespread dissemination of the study results to researchers, clinicians, patients and all relevant stakeholders. Additionally, the EPIC-PCD study team works closely with a team of patients with PCD who consult BEAT-PCD to ensure that all studies support their interests. Summaries of results in lay language will be disseminated to participants and national patient organisations by the EPIC-PCD data centre and the EPIC-PCD clinics, and to the relevant stakeholders and the public through the BEAT-PCD CRC website and social media.

## Data Availability

Data are available upon reasonable request.
